### Research questions

The main research question of this study is:□ Which digital intervention is most efficient for improving the stress management skills of health care and administrative personnel?

Regarding this main question, there might be some group-related differences to detect. Therefore, the following research questions should be answered:□ What are the differences in stress levels between nursing and administrative health personnel?□ What are the differences in sleep quality between nursing and administrative health personnel?□ How do intervention formats differ with regard to the effects on the processes of behavioral change?

Moreover, there are some outcome-related research questions:□ What is the association between the usage of mHealth intervention applications during working hours and stress levels of users?□ Is the effectiveness of the mHealth interventions determined by the age or gender of the participants?□ Is there a connection between stress and other outcomes such as back pain or physical activity levels?□ Do mHealth interventions contribute to a reduction in back pain?

Finally, the study should answer some acceptance and individualization related research questions:□ What is the rate of acceptance for the sensor-based mHealth interventions for nursing and administrative health personnel?□ What is the level of satisfaction for the sensor-based mHealth interventions for nursing and administrative health personnel?□ Do additional intervention requirements (e.g. for individualization) emerge as a result of the sensor screenings?□ What are the necessary requirements to ensure a long-term integration of sensor-based mHealth interventions to the daily routine of nursing and administrative health personnel?

## Methods

### Study design

The study is part of the project “Internet and app-based interventions to reduce stress in healthcare workers” (fitcor). The studies are conducted and described according to the Spirit checklist [80]. The study will be conducted as a longitudinal crossover design trial with five intervention groups and group comparisons (nurses vs administrative personnel). The study is part of the project “Internet and app-based interventions to reduce stress in healthcare workers” (fitcor). The studies are conducted and described according to the Spirit checklist [80]. The study will be conducted as a longitudinal crossover design trial with five intervention groups and group comparisons as described in Table 1 (nurses vs administrative personnel).

**Table 1 Tab1:**
[figure not shown]
Schedule of enrollment, interventions, and assessments: Recommendations for Interventional Trials (SPIRIT) chart of the enrollments and assessments during randomized controlled trials

The five intervention groups are as follows:Web-based digital stress management intervention (WBT only)Web-based and need-oriented digital stress management intervention (WBT + Need)Web-based and need-oriented digital stress management intervention with telephone coaching (WBT + Need + Coaching)App-based stress management interventions with sensory biofeedback (App + Biofeedback)App-based stress management intervention with sensory biofeedback and health report (App + Biofeedback + Report)

All participants of the intervention groups will receive a digital intervention. The waitlist control group will start the intervention after 8 weeks. Both, questionnaire and sensory data will be assessed:At baseline (*T*
_1_: pre-intervention/pre-waiting)At 8 weeks (*T*
_2_: post-intervention/post-waiting=pre-intervention)At 16 weeks (*T*
_3_: sustainability or post-intervention for waiting group; see Table 1).

### Participants

#### Eligibility and ethical approval

The crossover randomized controlled trial will include nursing staff and office workers aged 18 years or older from hospitals, stationary elderly care facilities, and ambulatory care providers. No clinical patients will be involved in the proposed study. Fluency in the German language as well as internet access via a smartphone device are prerequisites for study participation. All potential participants will be informed about the study and its procedure through a comprehensive informative video. The study is conducted in agreement with the principles of the Declaration of Helsinki and the guidelines of Good Clinical Practice. The recruitment of the participating nursing facilities involved cooperating health insurance companies, whereas the recruitment within the participating facilities will remain within the responsibility of the authors. Written informed consent will be obtained from all participants or their legal guardians before enrolment. Participants as well as their relatives or legal guardians can withdraw consent at any time. The local ethics committee of the TU Berlin, Germany, has approved the study protocol (No GR_14_20191217). The trial was registered at DRKS.de with registration number DRKS00021423 on 12 July 2021.

We used the program G*Power [81] to calculate the relevant sample size. To achieve the sample sizes required by power analysis with a β-error of 80% and an effect size of 0.25, we will need to include 700 participants. An effect size of 0.25 is considered a small effect, which is congruent with the literature on the effectiveness of eHealth/mHealth behavior change interventions [82, 83] and workplace health promotion interventions [84]. We expect a participation rate of 20% as this appeared to be a realistic participation rate in previous intervention studies in different small and middle-sized companies [85]. With an expected dropout rate of 20%, we will include additional 140 participants to ensure that the study results will still be eligible for data analyses.

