**Methods:**

We applied the SPIRIT (Standard Protocol Items: Recommendations for Interventional Trials) statement as a guideline for the present protocol. A randomized controlled trial will be conducted. There are five different intervention groups and one waiting control group. To achieve the sample sizes required by power analysis (G*Power) (β-error 80%; effect size 0.25), the sample sizes of the respective scenarios will be at best as follows: 336 care workers from hospitals, 192 administrative health personnel, 145 care workers from stationary elderly care homes, and 145 care workers from ambulatory care providers in Germany. Participants will randomly be assigned to one of five different intervention groups. A crossover design with a waiting control group is planned. Interventions will be accompanied by three measurement points, first a baseline measure, second a post-intervention measure directly after completion of the intervention, and a follow-up measure 6 weeks after completion of the intervention. At all three measurement points, perceived team conflict, work-related experience patterns, personality, satisfaction with internet-based training, and back pain will be assessed using questionnaires, as well as heart rate variability, sleep quality, and daily movement will be recorded using an advanced sensor.

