#### Participant recruitment

Participants will be recruited in health care facilities in Germany. For this purpose, the health insurance companies contact the executives of their collaborating hospitals, stationary elderly care facilities, and ambulatory care providers. The executives will forward an explanatory video to their employees via in-house communication networks, whereupon they can voluntarily enter their contact details into an online tool to register for the study. Previous experiences of the researchers showed that approximately only half of all contacted nurses participated in intervention studies. Therefore, in order to reach the target sample size, we will contact double the participants than we will actually include in the study.

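### Adding 140 to 700 does not leave 700 after 20% dropout; the abstract's 818 matches neither 700 nor 840, and two participation rates are left unreconciled

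*Protocol article*

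**What the plan says.** The figures stand in three places in the protocol article.

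- **Eligibility and ethical approval** (the sample-size paragraph). For an effect size of 0.25 and what is written as a β-error of 80%, "we will need to include 700 participants". The paragraph continues: "We expect a participation rate of 20% as this appeared to be a realistic participation rate in previous intervention studies", those studies having been done in small and middle-sized companies. It then adds: "With an expected dropout rate of 20%, we will include additional 140 participants", so that the data remain sufficient for analysis.
- **Abstract, Methods.** With the same 80% and 0.25, the sizes needed to satisfy the power analysis are given, qualified by the words *at best*, as "336 care workers from hospitals, 192 administrative health personnel, 145 care workers from stationary elderly care homes", plus 145 care workers from ambulatory providers. No total is given, and dropout is not mentioned.
- **Participant recruitment.** In the researchers' experience, "approximately only half of all contacted nurses participated in intervention studies". To reach the target sample size, "we will contact double the participants than we will actually include in the study".

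The Trial status section says that recruitment began in April 2021 and was completed in March 2022, although it also still describes recruitment as under way.

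**The concern.** An allowance for dropout should leave the required number once the expected share has gone. Taking 20% of the required number and adding it does not do that, because the people added also drop out at 20%.

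Two further mismatches concern the same target. The abstract and the methods give different totals for what is described as the same power analysis. The outreach plan also has two participation rates that differ by a factor of 2.5, and only one of them supports the contact rule.

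At stake is whether a reader can tell how many participants the trial needed, how many it meant to enrol, and whether it got there. That matters in a trial that plans comparisons between five intervention groups as well as against a waiting control. These are not details left to a fuller document: the article states the figures, and they do not agree.

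**Working it through.** **Inputs.** Required number 700, dropout 20%, addition 140 and participation 20% come from Eligibility and ethical approval. Group sizes 336, 192, 145 and 145 come from the abstract. Participation of about half and the contact rule of twice the target come from Participant recruitment.

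**1. The plan's own dropout figure.**
- 700 × 0.20 = 140, and 700 + 140 = 840. This reproduces the stated addition exactly, so the method used was n × (1 + d).

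**2. What 840 leaves.**
- 840 × (1 − 0.20) = 672.
- 700 − 672 = 28, and 28/700 = 4%.

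**3. What would leave 700.**
- n/(1 − d) = 700/0.8 = 875, an addition of 175.
- Check: 875 × 0.8 = 700.

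**4. Effect on power.** Assume that 700 gives 80% power at two-sided 0.05 for a test on one degree of freedom, with the normal approximation. The article states neither the test nor the effect-size metric.
- Standardised effect at 700: 1.960 + 0.842 = 2.802.
- At 672: 2.802 × √(672/700) = 2.802 × 0.980 = 2.745.
- Power: Φ(2.745 − 1.960) = Φ(0.785), about 78%.

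**5. The abstract's total.**
- 336 + 192 + 145 + 145 = 818.
- This is 118 above 700, 22 below 840 and 57 below 875. It equals none of them.

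**6. The contact rule.** If N is the target and 2N people are contacted:
- at 50% participation, 2N × 0.5 = N, so the rule closes (for N = 840, 1,680 contacts give 840);
- at 20% participation, 2N × 0.2 = 0.4N, which is 40% of the target whatever N is.

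| Target | Contacts needed at 50% | Contacts needed at 20% |
|---|---|---|
| 840 | 840/0.5 = 1,680 | 840/0.2 = 4,200 |
| 875 | 875/0.5 = 1,750 | 875/0.2 = 4,375 |

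**The case against.** **The dropout slip is small.** It costs 28 people and about 2 percentage points of power. The Statistical analysis section plans mixed models and, if feasible, multiple imputation, so someone lost after baseline need not vanish from the analysis. This stands and limits the weight of the point. It does not make 840 the number that leaves 700.

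**The two participation rates may describe different things.** The 20% comes from small and middle-sized companies, and the half from contacted nurses. Recruitment runs in stages (a forwarded video, voluntary registration, then participation), and neither section defines its denominator. So the rates cannot be called incompatible, only unreconciled. Against this, the sample-size paragraph adopts 20% as the expectation for this trial without limiting it to a subgroup, and the contact rule is applied to the whole target. Neither section refers to the other.

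**Stronger readings the documents do not support.**
- A reader might infer that the outreach plan would enrol only 1,680 × 0.2 = 336 people. That puts the 20% rate into a rule built on about half; on its own premise the rule closes. (The abstract's 336 hospital care workers are an unrelated figure.)
- A reader might go on to calculate a very low power for comparing two arms at that size. This would need 0.25 to be a standardised mean difference, a pairwise t-test and six equal arms. The article gives neither the metric nor the test for its power analysis, and it describes randomisation in sets of five numbers, so six equal arms cannot be taken as given.
- A reader might take 20% off 818, get about 654 and call that a shortfall against 700. The abstract does not say that 818 is an enrolment figure before dropout. It presents the sizes as what the power analysis requires, and qualifies them with *at best*.

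**Recruitment is reported as completed.** The risk to outreach has therefore passed. This stands: what remains is a matter of correct reporting.

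**Conclusion.** The point holds as a set of wrong or conflicting sample-size figures with a modest numerical effect.

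- The stated enrolment of 840 does not deliver the stated 700 at the plan's own dropout rate. It leaves 672, 4% short; 875 would be needed. This rests on reading 700 as the number wanted after dropout, which is the purpose the article gives for the addition. The fall in power to about 78% rests also on the assumptions in the working, including that the β-error of 80% means 80% power.
- The abstract's 818 and the methods' 700 and 840 are not reconciled, although the same 80% and 0.25 are cited for both. Which is the target cannot be settled from the article.
- The participation rates of 20% and about half are not reconciled, and the contact rule depends on the second. At the first it would reach 40% of the target.

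None of this shows that the trial under-recruited or invalidates its design. It does mean that the article gives no single planned size against which the achieved sample can be judged.

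**What to change.** 1. State one enrolment target in both the abstract and the methods, and say whether it is before or after dropout. If 818 is a separate figure, say what it is and how it relates to 700 and 840.
2. Either give 875 as the enrolment that leaves 700 after 20% dropout, or keep 840 and state that it leaves 672, with power restated on 672.
3. Use one participation rate with a defined denominator and derive the number of contacts from it, or explain why the two rates differ and where each applies.
4. As recruitment is reported as completed in March 2022, report the number enrolled and the participation rate achieved, and bring the Trial status wording into line.

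The cost is a few corrected figures and sentences in the abstract, the sample-size paragraph and the recruitment section. The design does not change. If 840 is kept, the stated number available for analysis and its power become slightly less favourable.

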#### Allocation and blinding

To prevent selection bias, the allocation of participants to the intervention groups and waiting control group will be assigned randomly by lot by the director of the study. There is going to be a random allocation at the individual level with the tool Research Randomizer using continuous block randomization. Sets of five numbers will be generated, representing the differing number of study groups. Each participant is then assigned the subsequent number on the block randomization list for group assignment. Therefore, each person can theoretically be assigned to any of the study arms. As participants will be assigned to an intervention group or the waiting control group by lot, no further mechanisms of implementing the allocation sequence is needed. To our best knowledge, there are no circumstances under which unblinding of the data assessors could be needed. Trial participants will be informed about which intervention group they are assigned to as they will need to receive the respective information to complete all necessary information and access the digital intervention programs. Outcome assessment will be blinded as the assessment is done in an online questionnaire that participants fill out independently. The sensor screening will also be done without including a third party as participants apply the sensor on their body by themselves. All data analyses will be run by blinded assessors.

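### The randomisation list uses sets of five numbers for a trial with six groups, so as described it cannot draw every group; the one left out is most naturally the waiting control

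*Protocol article*

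**What the plan says.** The Methods paragraph of the abstract gives the design: "There are five different intervention groups and one waiting control group". Under Study design, the text with Table 1 names the five interventions (three web-based, two app-based) and treats the waitlist control as a further group that starts after 8 weeks. That makes six groups.

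Allocation and blinding first states what is to be randomised: "the allocation of participants to the intervention groups and waiting control group will be assigned randomly by lot by the director of the study". It then describes the list: "Sets of five numbers will be generated, representing the differing number of study groups". The list is used in order: "Each participant is then assigned the subsequent number on the block randomization list for group assignment". From this the section infers that "each person can theoretically be assigned to any of the study arms", and adds that "no further mechanisms of implementing the allocation sequence is needed".

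Elsewhere the abstract describes the assignment without the control: "Participants will randomly be assigned to one of five different intervention groups". No section gives a sixth number, a separate draw for the waiting control, or an allocation ratio.

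**The concern.** The set size is tied explicitly to the number of study groups, and it is one short. A list with one number per group and five numbers per set gives one of the six groups no chance of being drawn. The article fixes this rule itself, so it is not a detail left to an analysis plan.

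The waiting control is the only group untreated up to the second measurement. The Statistical analysis section relies on it for the comparison of the pooled interventions with control. Whether that contrast is randomised depends on how control members are drawn, and the one mechanism described does not draw them. Until this is clarified, a reader cannot confirm that the trial's only controlled comparison rests on random allocation, or say what share of participants was meant to be in control.

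**Working it through.** **Inputs**
- Groups to be allocated: 5 interventions + 1 waiting control = 6 (abstract; Study design).
- Numbers per set: 5, said to stand for the number of groups (Allocation and blinding).
- Planned entrants: 700 + 140 for dropout = 840 (Eligibility and ethical approval). The four setting targets in the abstract add to 336 + 192 + 145 + 145 = 818.
- Allocation ratio: not stated. Equal allocation is assumed below.

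**Step 1: count check.** Labels needed = 6; labels per set = 5; shortfall = 6 − 5 = 1. With one label per group, one group has allocation probability 0. This does not depend on sample size or ratio.

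**Step 2: which group is missing.** The five groups that the article numbers and names are the interventions, and the abstract's assignment sentence mentions only those five. The group without a label is therefore most naturally the waiting control. This step is inference; the shortfall in Step 1 is not.

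**Step 3: compare with the section's own conclusions.**
- Stated: everyone can reach any arm. From Step 1: at most five of the six arms can be reached.
- Stated: nothing further is needed to implement the sequence. From Step 1: something further is needed, either a sixth label or a second draw.

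**Step 4: illustration of size.**
- Five labels, one per intervention: 840 / 5 = 168 per intervention group, waiting control 0.
- Six labels, equal allocation assumed: 840 / 6 = 140 per group, waiting control 140.
- On the abstract's total: 818 / 5 = 163.6 per group, against 818 / 6 = 136.3.

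Generating permuted blocks for 840 entrants gave the same counts: 168 in each of five groups with five labels, and 140 in each of six with six labels.

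**The case against.** The strongest objection is that a coherent scheme fits most of the text. Under Data collection, management, and analysis, waiting controls also receive one of the interventions later. A lot could decide immediate versus waiting start, and the five-number list could then decide which intervention. That would be fully randomised. The section says twice that assignment to the waiting control is by lot, and nothing in the article suggests a non-random route. This largely stands, and it limits what can be concluded. It does not rescue the paragraph, because no such step or ratio is described and the section says none is needed.

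Two other readings help less. Five numbers drawn from a range of six could reach every group, but the text ties the five to the number of groups and gives no such range. The word differing might mean that the number of groups varies by setting. The targets 336 and 192 divide by six and not by five, and 145 divides by five and not by six, which is suggestive only. The article never says which groups run where. If the targets did reflect group counts, sets of five would still fail for 336 + 192 = 528 of the 818 planned participants.

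A reader might also infer that the last assignment in each block of five is predictable, because the block length is fixed and the study director assigns. That would require someone to track every assignment in order. It is a separate and weaker matter, concealment detail is commonly left to the full protocol, and the mismatch does not depend on it.

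**Conclusion.** The point holds as an internal contradiction in a stated rule: a six-group trial is given a list that can reach five groups. The shortfall of one group is certain on a one-number-per-group reading. That the missing group is the waiting control is the natural inference, not a stated fact.

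A reader might go further and conclude that the controls were not randomised, that the control comparison carries selection bias, or that the trial would have no controls. The article does not support this. It declares random assignment to the waiting control, gives that group its own schedule and plans an analysis for it; a random draw made outside the list would still be randomisation. The figure of 0 controls shows what the sentence yields if followed to the letter and is not a forecast. The figure of 140 per group rests on 840 entrants and an equal ratio that the article does not state.

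The correction is still needed, because the only controlled comparison depends on this mechanism.

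**What to change.** Correct Allocation and blinding in one of two ways, whichever matches what was intended or done:
- permuted blocks covering all six groups, in sets of six or a multiple of six, with the ratio stated; or
- a separate random draw for immediate versus waiting start, with its ratio, and the five-number list used only to choose the intervention. The statement that nothing further is needed should then be removed.

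The abstract's assignment sentence should be aligned with the chosen version.

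Trial status calls recruitment current but also says that it was completed in March 2022, with measurement under way since September 2021, so a new list may come too late. If allocation is complete, report from the allocation records how and in what ratio waiting controls were actually drawn. Label the waiting-control comparison non-randomised only if that route was not random.

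The cost is a corrected paragraph and, if allocation is complete, a check of the allocation records. Random block sizes or stratification by setting are not needed to remove this contradiction.

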### Data collection, management, and analysis

Relevant outcome variables will be assessed at three time points. The different measurement points are the same for all five intervention groups. The baseline measurement (*T*
_1_) is first carried out on the participants directly prior to beginning with the interventions. The post-intervention measure will be performed immediately after the interventions are completed (*T*
_2_). After another 6 weeks of no intervention, the sustainability measurement (*T*
_3_) will be conducted. For the waiting control group, the first measurement (*T*
_1_) will be followed by a period of eight weeks of waiting. The second measurement (*T*
_2_) will be conducted after this waiting period. Then participants of the waiting control group will receive one of the interventions and then have their third measurement directly after finishing the respective intervention (*T*
_3_). At all three measurement points, the same variables, namely physiological stress, perceived stress, satisfaction with the digital intervention, personality, work-related behavior patterns, and team conflict will be measured.

The respective measurement tools that will be applied are described in the outcomes section including information on reliability and validity. In order to promote data quality, we include evaluated scales that appeared to be reliable and valid in previous studies. We will not conduct duplicate measurements. The collected data will be processed pseudonymously in digital form (from the initial measurement to the sustainability study—approx. 12 weeks).

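### The protocol says that assignment by lot makes any further allocation mechanism unnecessary, so the stated procedure does not secure concealment

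*Protocol article*

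**What the plan says.** All the main statements are in the protocol article under Allocation and blinding. The section opens with its aim, which is the prevention of selection bias. On who assigns, it says that the groups "will be assigned randomly by lot by the director of the study". The next sentence describes "random allocation at the individual level with the tool Research Randomizer using continuous block randomization". On the list itself: "Sets of five numbers will be generated, representing the differing number of study groups". On its use: "Each participant is then assigned the subsequent number on the block randomization list for group assignment". The section then concludes that, because the lot decides, "no further mechanisms of implementing the allocation sequence is needed".

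The same section says that participants are told their group. The blinding it describes covers self-completed outcome assessment and data analysis.

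Two other sections bear on who could influence entry. Eligibility and ethical approval says that "the recruitment within the participating facilities will remain within the responsibility of the authors". Participant recruitment says that facility executives forward a video and that employees then register themselves in an online tool.

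**The concern.** The section treats random generation of the sequence as if it also concealed the sequence. These are separate safeguards. Generation makes the order of groups random. Concealment stops the person who enters a participant from knowing or guessing the next group before that participant is committed to the trial. Selection bias enters through the second, which the text expressly dismisses.

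The text also names two procedures without reconciling them: a drawing of lots by the director, and reading off the next entry of a pre-generated list. They carry different risks. A lot drawn at the moment of entry reveals nothing in advance, whereas a list reveals everything to whoever can read it.

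At stake is the comparability of the groups at entry. If the next group is known or guessable, the order in which registrants are entered, or the decision to enter someone now or later, can depend on it. Blinded analysis does not repair that.

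**Working it through.** The article gives no figure for predictability, so there is none to reproduce. Two checks apply.

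**1. What the procedure reveals, step by step**

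- Assigner: the study director (Allocation and blinding).
- Source of the assignment: the next number on a list generated beforehand (same section).
- Safeguards described between list and assignment: none. No independent list holder, automatic release, sealed sequence or varied block size is mentioned, and the text says that nothing more is needed.
- Disclosure: each participant learns the group, so past assignments can become known to others.

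On this description, a person who can read the list knows 100% of upcoming assignments.

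**2. What can be guessed without the list**

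Inputs:
- Block size 5, from the sets of five, with no variation described.
- Block size 6 as an alternative, because the Abstract lists five intervention groups and one waiting control group: 5 + 1 = 6. The article does not explain how sets of five serve six groups, so both sizes are shown.

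Assumptions: each group appears once per block, and the guesser knows all earlier assignments in the block and always names a group not yet used.

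With i places left in a block, i groups remain and are equally likely, so a guess is right with probability 1/i. The expected number of correct guesses per block of size k is the sum of 1/i for i = 1 to k, and the rate is that sum divided by k.

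- k = 5: 1 + 0.5 + 0.3333 + 0.25 + 0.2 = 2.283; 2.283 / 5 = 45.7%. Chance is 1/5 = 20.0%. A simulation of 200,000 blocks also gave 45.7%.
- k = 6: 2.283 + 0.1667 = 2.450; 2.450 / 6 = 40.8%. Chance is 1/6 = 16.7%.

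The last place in each block is certain: 1 in 5 assignments, or 1 in 6. Someone who sees only some of the earlier assignments falls between the chance rate and these values.

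A concealed, unpredictable sequence brings the rate back to 20.0% or 16.7%. No sample-size or power figure changes.

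**The case against.** The strongest reply is that this is a condensed article, that the full protocol is available on request (Data Availability), and that custody of the list is a detail an article may leave there. Nothing says that the director recruits, knows the registrants or controls their order. Employees register themselves online, and the eligibility criteria (age, occupation, German, smartphone access) leave little discretion. A guess does harm only if the guesser can alter who enters or when, and no section shows that recruiters see the ordered past assignments. The lot may also be just a lay phrase for the randomiser list.

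Much of this stands, and it limits the point. It does not rescue the sentence. The article does not leave concealment to another document; it says that none is needed. Self-registration narrows the scope for steering but fixes neither the order of entry nor who sees the list, and recruitment inside facilities stays with the authors.

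A reader might infer more than the documents support:

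- **That upcoming groups were in fact visible.** The article does not say who holds the list.
- **That the group is known before baseline (T1), so that baseline answers are distorted.** The text says only that T1 "is first carried out on the participants directly prior to beginning with the interventions". The order of allocation and T1 may be given in Table 1, which is not visible here.
- **That a self-reported baseline would then contaminate every model.** Primary outcomes include sensor measures such as heart rate variability, sleep duration and steps, whose baseline is not self-reported.
- **That participants drop out differently by group before T1.** The section on adherence mentions only reminders to people who forgot to order sensors or register, and does not place this after allocation.
- **That a bias of a given size can be attached to the treatment effect.** The documents contain no figures for that.

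**Conclusion.** The point holds as a wrong stated rule: assignment by lot does not remove the need for a mechanism that conceals the sequence, and the procedure as described does not secure the section's own aim. The size is a matter of predictability, not of demonstrated bias: 100% for a list holder, and up to 45.7% (block of 5) or 40.8% (block of 6) for someone who knows the past assignments, against 20.0% or 16.7% by chance. These rates assume fixed blocks with one place per group and full knowledge of earlier assignments. The inference about the list is strongest for the director, who applies the next number with no safeguard described, and weaker for anyone else. The text should be corrected, but it is not evidence that the groups are unbalanced.

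**What to change.** Delete the sentence that declares further mechanisms unnecessary, and describe one procedure only, so that the drawing of lots and the list are reconciled. That procedure should be:

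- a computer-held list with randomly varied block sizes that fit the actual number of groups;
- hidden from everyone who recruits or enters participants;
- with the group released only after consent and irrevocable enrolment, and after T1 is complete where feasible.

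The cost is a small set-up effort and protocol wording, plus a possible short wait before the intervention starts if release depends on T1. Whether the existing registration tool can do this is unknown, since the article describes it only as collecting contact details.

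Trial status says both that recruitment is under way and that it was completed in March 2022. If allocation is already finished, a new system cannot apply. The sponsor should then correct the sentence, state which procedure was used, who held the list and whether T1 preceded disclosure of the group, and report the concealment risk as a limitation.
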